Research on recovery shows that 38 and 78% of patients with PDOC due to traumatic brain injury (TBI) regain (minimal) consciousness at respectively 3 and 12 months post injury [2]. In patients with non-traumatic brain injury (NTBI) only 17% regains consciousness at 8 months post injury [2]. Aidinoff et al. [14] demonstrated an improvement in survival and recovery of consciousness in UWS patients over the last two decades after EIN, and similar outcomes for both TBI and NTBI UWS. These outcomes suggest that improvements in acute medical care and EIN have contributed to advances in UWS care. Treatment started within 8 weeks after injury is associated with better outcomes in terms of LOC and functioning, gained in a faster pace than treatment started after 8 weeks [15–17]. In patients with PDOC of mixed aetiology with a mean time follow-up of 5 years, 40% of survivors reached functional independence, while 42% of patients able to respond to a self-report questionnaire, reported a poor quality of life [18]. The EIN programme in the Netherlands has been studied before; in patients aged < 25 years recovery of consciousness occurred in two-thirds at the end of the EIN programme [19] and two-thirds of the patients who were fully conscious at discharge were able to live independently after 10–12 years [20].

Prognostic factors associated with better recovery from PDOC are younger age at onset, traumatic aetiology, less severe comorbidities and less severe neurological impairment, i.e. higher level of consciousness at admission to EIN [2, 4, 15, 21–25]. However, most studies on recovery after PDOC suffer from methodological issues, such as a retrospective design [2] and variability in clinical decision making in acute care [2]. Further, research on outcomes after PDOC often fails to discriminate between diagnostic subtypes (UWS or MCS), aetiology and the time since injury [2]. Furthermore, data on quality of life, costs and cost-effectiveness of rehabilitation programmes, and caregiver burden are limited.

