**Inclusion criteria**	
Age16 years or older	
PDOC (UWS or MCS) lasting > 4 weeks and < 6 months at admission to EIN	
First-time newly acquired non-progressive brain injury of any aetiology	
Weaned from ventilator	
Medically stable, as judged by the treating rehabilitation physician	

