### Statistical analysis

Descriptive statistics will be used to present the outcomes of the study parameters and the socio-demographic data. Means and standard deviations will be calculated for variables on an interval scale and medians and interquartile ranges for ordinal variables. Proportions will be calculated for nominal variables.

Subgroup analyses will be performed for patients presenting in UWS versus MCS at baseline and for traumatic versus non-traumatic disorders of consciousness.

The proportions of patients transitioning from UWS to MCS and emergence from MCS to the conscious state will be calculated during and after EIN.

The course of recovery of consciousness (yes/no) over time will be analysed using Generalized Estimating Equations (GEE) analysis for logistic outcomes on an intention-to-treat basis. Assuming that data are missing at random, data imputation is unnecessary in GEE analysis; all observations are taken into account in contrast to complete case analyses. Recovery (yes/no) at each time point will be included as the dependent variable in the GEE model. Separate models will be generated for transitions from UWS to MCS and from MCS to the fully conscious state based on the CRS-R. Independent variables that will be added one by one to the models, include- measurement time (weeks), traumatic vs. non-traumatic aetiology, age at injury, and complications (yes/no or number). Significant predictors (*p* < 0.05) will be included in a multivariable model using a Bonferonni correction, dividing the significance level (alpha< 0.05) by the number of predictors included in the model.

Also using GEE analysis, the course of quality of life (EQ-5D-5L and Qolibri) and participation (CIQ) over time will be analysed using separate linear outcome models. The effects of time, cognitive (MoCa), behavioural (NPI), emotional (HADS), and motor status (FIM), and level of disability (DRS) and discomfort (NCS) on quality of life or participation during follow-up will be studied by adding these time-dependent variables (one by one) as independent variables to the models. Significant predictors (*p* < 0.05) will be added into a multivariable GEE-model to study the independence of these potential predictors on the outcomes using the Bonferroni correction.

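### The recovery models do not name time since injury at admission as a predictor, and they handle admission consciousness only by class (UWS or MCS)

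*Protocol article*

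**What the plan says.** The Statistical analysis section models recovery of consciousness (yes/no at each time point) by logistic GEE, separately for UWS to MCS and for MCS to full consciousness. It introduces the predictors with "Independent variables that will be added one by one to the models, include" and then names "measurement time (weeks), traumatic vs. non-traumatic aetiology, age at injury, and complications (yes/no or number". Those with p < 0.05 go into a multivariable model, judged after "dividing the significance level (alpha< 0.05) by the number of predictors included in the model". The same section plans subgroup analyses by UWS versus MCS at baseline and by traumatic versus non-traumatic cause.

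The Background gives the reasons for the study. Among the factors associated with better recovery it lists "less severe neurological impairment, i.e. higher level of consciousness at admission to EIN". On timing it says "Treatment started within 8 weeks after injury is associated with better outcomes in terms of LOC and functioning". Its complaint about earlier outcome research is that it often "fails to discriminate between diagnostic subtypes (UWS or MCS), aetiology and the time since injury".

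Table 1 admits patients with "PDOC (UWS or MCS) lasting > 4 weeks and < 6 months at admission to EIN". Under Data collection, the later measurements at weeks 28, 40, 52 and 104 are counted from inclusion.

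**The concern.** The Background names three things that earlier work failed to separate: subtype, aetiology and time since injury. The analysis takes up the first two. The third appears in no model, no subgroup and no time axis.

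This matters because the study aims to identify predictors of recovery, to benchmark the programme and to improve outcome prediction. A patient admitted just after 4 weeks and one admitted just before 6 months are not at the same point in recovery: the second has already gone months without regaining consciousness. If late admission is more common in one aetiology, in older patients or in those with complications, part of the effect of late admission will be reported as an effect of those predictors. The same applies to CRS-R score at admission within UWS or within MCS, on which the models place no term.

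**Working it through.** The plan has no figure of its own to reproduce here. The target of 72 patients is stated without effect size or power.

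**1. Factors named in the Background against terms in the recovery models**

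- Aetiology: named predictor and subgroup.
- Age: named predictor.
- Diagnostic subtype at admission: subgroup, and separate transition models. There is no score within a class.
- Time since injury, or early versus late start: no term, no subgroup.

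**2. Whether measurement time can stand in for time since injury**

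Inputs: entry limits of 4 weeks and 6 months (about 26 weeks) from Table 1, and measurement weeks from Data collection. Assumption: duration of the disorder at admission is counted from the injury. Time since injury = measurement week + time since injury at admission.

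- Admission: 0 + 4 = 4 to 0 + 26 = 26 weeks
- Week 14: 14 + 4 = 18 to 14 + 26 = 40 weeks
- Week 28: 28 + 4 = 32 to 28 + 26 = 54 weeks
- Week 52: 52 + 4 = 56 to 52 + 26 = 78 weeks

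The width is always 26 − 4 = 22 weeks, so measurement time carries no information on a patient's place in this range. The window also spans the 8-week boundary cited in the Background. The Discussion places most functional recovery within 1 year of injury, and the week 28 record can fall on either side of that point.

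**3. Possible size of confounding (illustration; all inputs assumed)**

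Take a two-level admission factor, aetiology with no true effect, recovery of 25% at the unfavourable level, and an odds ratio (OR) of 2 to 5 for the factor. If a share m of an aetiology group has the favourable level, recovery in that group is m × p1 + (1 − m) × 0.25. Here p1 = 0.40 for OR 2 (odds 1/3 × 2 = 2/3) and p1 = 0.625 for OR 5 (odds 1/3 × 5 = 5/3).

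- Shares 60% and 40%, OR 2: 0.340 and 0.310, crude aetiology OR (0.340/0.660)/(0.310/0.690) = 1.15
- Shares 60% and 40%, OR 5: 0.475 and 0.400, crude OR 1.36
- Shares 70% and 30%, OR 2: 0.355 and 0.295, crude OR 1.32
- Shares 70% and 30%, OR 5: 0.5125 and 0.3625, crude OR 1.85
- Equal shares: crude OR 1.0

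The arithmetic is the same whether the factor is early versus late admission or higher versus lower CRS-R within a class.

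**4. Cost of adding terms**

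Assume a recovery proportion between 17% and 67%, a range suggested by figures in the Background. Patients with the rarer outcome number N × min(p, 1 − p). Within the range, p = 0.17 and p = 0.38 gave the lowest and highest of the values tried (p = 0.67 lies between them):

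- N = 72: 72 × 0.17 = 12.2 and 72 × 0.38 = 27.4. Per predictor: 3.1 to 6.8 with four terms, 2.4 to 5.5 with five, 2.0 to 4.6 with six.
- N = 36 in one transition model (assumed): 6.1 and 13.7. Per predictor: 1.5 to 3.4 with four, 1.2 to 2.7 with five, 1.0 to 2.3 with six.

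If every term counted in the divisor, the Bonferroni threshold would go from 0.05/4 = 0.0125 to 0.05/6 = 0.0083.

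**The case against.** Four points can be made for the plan.

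*Admission consciousness is in the analysis.* This stands in part. A reader might infer that the plan ignores it, but the baseline subgroups and the separate transition models both use it. What remains is narrower: no CRS-R score or finer grade is used within a class, and the text does not say whether a patient admitted in UWS who reaches MCS then joins the second model beside those admitted in MCS. Neither device touches time since injury.

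*The list may be open, and details may sit in an analysis plan that is not shown.* The verb that introduces the list does leave room. But the article does not defer to another document: it states a list and a selection rule. For the caregiver models it names level of consciousness explicitly, so covariates are named where they are intended. The point is that the stated list does not match the stated rationale, not that detail is missing.

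*No imbalance is shown.* This stands. The documents give no distribution of admission timing or CRS-R score by aetiology, age or complications, and with equal shares the illustration gives an odds ratio of 1.0. The confounding is a risk, not a demonstrated fact.

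*More terms strain a small model.* This also stands, as step 4 of the working shows, and it shapes the fix.

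**Conclusion.** The point holds, most firmly for time since injury. The protocol criticises others for not separating it, reports that early start goes with better outcomes, admits patients across a window of about 22 weeks, and then uses it nowhere in the recovery analysis. For admission consciousness the gap is limited to differences within UWS and within MCS.

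The 22 weeks are the widest spread that eligibility allows, on the assumption that duration is counted from injury; the actual spread may be much smaller. The odds ratios of 1.15 to 1.85 rest wholly on assumed inputs.

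Three stronger readings are not supported:

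- That the protocol treats these factors as decisive or as the strongest predictors. It says only that they are associated with outcome and does not rank them.
- That the planned effects are confounded as a matter of fact. That depends on imbalances the documents do not report.
- That leaving the factors out costs precision. In a logistic model, adding a prognostic covariate generally raises the standard errors of the other coefficients, so the case for adjustment rests on confounding and interpretation.

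**What to change.** In both transition models, pre-specify weeks from injury to EIN admission as a continuous covariate that stays in whatever its univariable p-value. Retain baseline CRS-R total score in the same way where the number of outcomes allows. Describe both as adjustment terms and leave them out of the Bonferroni divisor, so that the threshold for the predictors under study does not fall because of them.

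No new measurement appears to be needed. CRS-R is the plan's instrument for level of consciousness, which is assessed weekly during EIN, with structured collection from the start of the programme. Time since injury is not listed as a collected item in the text available, but the entry window and age at injury imply that the date is known; this should be confirmed.

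The cost is one or two more parameters in models with few outcomes per predictor. Keep the other candidates few, or use penalised estimation in place of one-by-one screening. If only one term can be afforded, time since injury should come first, because nothing else in the plan covers it.

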### EIN programme

The EIN programme is a subacute medical rehabilitation programme of 14 weeks (or less when recovery of consciousness occurs earlier) and meets the guideline recommendations for patients with PDOC published by the American Academy of Neurology [26]. An interdisciplinary rehabilitation team of a rehabilitation physician, a physician assistant, a neuropsychologist, cognitive rehabilitation therapists, physiotherapists, occupational therapists, speech therapists, nursing staff, dietician, and social worker uses an integrated approach in a 24/7 setting [19] with a minimum duration of 120 min therapy per day in which daily routines are built in together with a structured scheme of therapy and rest. The program is focused on optimizing the metabolic state, nourishment, respiration and skin condition, as well as diminishing the risk of infections and quick removal of invasive devices, like a tracheostomy tube or a urinary catheter, and recovery of the normal circadian cycle. Pharmacological treatments and structured stimulation of all sensory modalities (vision, hearing, smell, taste, touch, posture and motion, pain and temperature) aim to generate maximal arousal. As soon as the patient shows any voluntary reactions, reflecting a change from UWS into MCS, the focus of treatment changes from stimulation to training of cognitive functions. Motor rehabilitation aimed at optimising postural and motor activity helps restore bodily integrity and reduces the risk of complications (e.g., infection, thrombo-embolic complications, skin breakdown). For patients who reach MCS, increased time is spent on training mobility and self-care. Coping and self-efficacy of caregivers are addressed with psychoeducation, counselling and hands-on training in handling the patient.

After EIN, patients are discharged to 1) a regular neurorehabilitation setting in case of full recovery of consciousness and the ability to participate in a rehabilitation programme as judged by the rehabilitation physician, 2) to skilled nursing facilities, 3) sheltered housing or 4) possibly home (Fig. 2). Some skilled nursing facilities offer a prolonged intensive neurorehabilitation programme (PIN) for further recovery of consciousness during a period of up to 24 months post-injury. EIN is part of an academic network of expertise (EENnaComa) in which various healthcare institutes specialised in post-acute and long-term care of PDOC patients and their families are united.

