### Data collection

In 4 years we aim to include 72 patients. Structured data collection (Fig. 3) will take place at the start of the EIN programme at week 5, 10, and at EIN discharge (week 14). LOC assessment and registration of complications will be done weekly.

After discharge from EIN, follow-up measurements are planned at 28, 40, 52, and 104 weeks post-inclusion. These will take place at the patients’ actual health-care institution or residence.

All measurements conducted during the EIN programme are performed by trained members of the rehabilitation team. Follow-up measurements are performed by a trained research assistant.

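### In the MCS-to-conscious model, a plain count or yes/no of complications depends on length of stay, which recovery itself can shorten, so complications may look harmful with no true effect

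*Protocol article*

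**What the plan says.** Three parts of the protocol article bear on this.

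- **Statistical analysis.** The outcome is repeated: "Recovery (yes/no) at each time point will be included as the dependent variable in the GEE model". There are two recovery models: "Separate models will be generated for transitions from UWS to MCS and from MCS to the fully conscious state based on the CRS-R". The candidate predictors end with "and complications (yes/no or number". The covariates of the quality-of-life and participation models are called time-dependent in the next paragraph; complications in the recovery models are not.
- **EIN programme.** The stay is a "programme of 14 weeks (or less when recovery of consciousness occurs earlier". Reaching MCS is not an exit point, since treatment goes on with a different emphasis: "For patients who reach MCS, increased time is spent on training mobility and self-care".
- **Data collection.** "LOC assessment and registration of complications will be done weekly" closes the paragraph on measurement during EIN. The next paragraph begins "After discharge from EIN, follow-up measurements are planned at 28, 40, 52, and 104 weeks post-inclusion" and does not mention complications. The measurement plan (Fig. 3) is not visible in the text available.

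**The concern.** A patient who regains consciousness in week 8 may leave EIN then; one who does not stays to week 14. If complications are counted over the stay, the second patient has 6 more weeks in which to have one. The predictor is then partly a record of length of stay, and length of stay is partly set by the outcome. Reverse causation of this kind makes complications look harmful even if they have no effect on recovery.

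Preventing complications is a stated aim of EIN, and predictors of recovery are a main product of the study, meant to help improve the programme. A spurious coefficient would bear directly on that aim. Selection at p<0.05 followed by a Bonferroni correction does not protect against it, because the correction limits chance findings and leaves bias untouched.

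**Working it through.** The article gives no complication rate, no effect size and no power calculation, so there is no figure of the plan to reproduce. All rates and recovery proportions below are assumptions.

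**1. Two-group illustration.** Let complications arise at a constant rate r per week, unrelated to recovery. Recoverers leave at week e, the others at week 14.

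- P(any complication by week t) = 1 − exp(−r·t), so the odds are exp(r·t) − 1.
- Spurious odds ratio = [exp(r·e) − 1] / [exp(14r) − 1].

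| r per week | e (week) | Calculation | Odds ratio |
|---|---|---|---|
| 0.1 | 8 | 1.23 / 3.06 | 0.40 |
| 0.05 | 10 | 0.649 / 1.014 | 0.64 |
| 0.3 | 6 | 5.05 / 65.7 | 0.08 |

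In the first row the proportions with any complication are 55% and 75%, and the mean numbers are 0.1 × 8 = 0.8 and 0.1 × 14 = 1.4. The other two rows are the extremes of a grid with r from 0.05 to 0.3 and e from 6 to 10.

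**2. Closer to the planned analysis.** A simulation with no true effect used 72 patients, visits at weeks 5, 10, 14, 28, 40, 52 and 104, and a logistic GEE of recovery on complications and log time. The working correlation was independence, with robust standard errors. Registration stopped at recovery or week 14. Assumed: recovery by week 14 of 20, 40 or 60%; 0.1 or 0.3 complications per week; 200 runs per setting.

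| Coding, MCS-to-conscious model | Odds ratio | Falsely harmful at p<0.05 |
|---|---|---|
| Total number over EIN | 0.53–0.71 per complication | 46–100% |
| Yes/no over EIN | 0.23–0.44 at 0.1/week; about 0.05 at 0.3/week | 41–96% |
| Number accumulated to each visit | 0.57–0.76 per complication | 38–99% |

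At 0.3 per week few patients have no complication, so only 157 to 173 of 200 yes/no fits were usable.

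**3. Variations** (40% recovery, 0.3 per week, total number over EIN):

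- Discharge 2 or 4 weeks after recovery: odds ratio 0.71 or 0.78, falsely harmful in 89% or 66%.
- Death at 1 to 3% per week: odds ratio 0.53 to 0.61, falsely harmful in 97 to 99%.

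**4. UWS-to-MCS model.** With 50% assumed to reach MCS by week 14 and EIN ending only at full consciousness, the odds ratio is 0.93 (72 patients) or 0.94 (36 patients), falsely harmful in 7% or 6%. That is close to nominal.

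**5. Equal windows remove the bias.**

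- Complications in weeks 1–5, among patients still in EIN at week 5: odds ratio 0.99–1.03, significant in 4.5–7.5%.
- A fixed 14 weeks whatever the discharge date: odds ratio 0.98–1.02, significant in 3.5–8.5%.
- Per-interval coding with registration through week 104: odds ratio 1.00, significant in 4%.

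With 200 runs, the standard error of a 5% rate is √(0.05 × 0.95 / 200) = 1.5 percentage points.

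**The case against.** A reader might infer that recovery always ends registration, and that complications will therefore look harmful in every recovery model. The document does not support that reading, for these reasons.

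- **Coding is open.** With recovery modelled at each time point and complications registered weekly, a time-updated covariate fits the wording too. This stands, and it makes the point conditional. Time-updating alone is not enough, though: per-interval counts up to week 14, with intervals after discharge filled as zero, gave an odds ratio of 0.33 and false harm in every run (40% recovery, 0.3 per week). Using observed intervals only gave 0.93 and 3.5%.
- **The end of registration is not stated.** The text places weekly registration in the EIN paragraph, but Fig. 3 is not shown, and complications are a named outcome of a study with 24 months of follow-up. Registration after discharge cannot be excluded. If it continues, the window is less truncated, but a total that includes complications after recovery still breaks the time order.
- **UWS to MCS.** Reaching MCS does not end EIN, so this mechanism hardly touches that model. This stands in full.
- **The illustration is simpler than the plan.** It is one comparison of two groups. Patients who recover after week 14 have full exposure, discharge may lag recovery, and some listed complications, such as contractures and spasticity, are lasting states and not events at a constant rate. These points change the size. In the simulated GEE, late recovery and a discharge lag left the direction unchanged.

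That the window of a covariate is often left to a fuller document is a fair remark. Here, however, the article names two codings, and in their plain form both are open to this bias.

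**Conclusion.** The concern holds for the MCS-to-conscious model, on two conditions: complications are entered as a stay total, a cumulative total or ever/never, and registration ends at or soon after discharge. That is the plainest reading of the text, but not the only one. Under it, the association is biased towards harm with no true effect. The two-group odds ratio is 0.08 to 0.64 over the assumed range. In the simulated GEE it is 0.53 to 0.71 per complication for a stay total, moving to 0.71 or 0.78 in one setting (from 0.62) when discharge lags recovery by 2 or 4 weeks.

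The false-positive percentages depend on the assumed rates and on placing all 72 patients in this one model; with fewer patients they would be lower. The UWS-to-MCS model is little affected by this mechanism. There, the remaining requirement is one of time order: a complication after the transition should not count as its predictor.

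**What to change.** In the recovery models, replace the plain coding with one of these:

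- **Lagged, time-updated covariate.** Presence or number of complications in a fixed window before each assessment interval, among patients not yet recovered at its start. Intervals without registration are missing, not zero.
- **Landmark.** Complications in weeks 1–5 as predictor of later recovery, among patients still in PDOC at week 5.

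Both ensure that the complication precedes the outcome, in the UWS-to-MCS model as well. State whether registration continues after discharge; if it does not, the landmark is the simpler choice for the visits from week 28 on. Report descriptive totals as a rate per patient-week.

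The cost is analysis wording only, since weekly registration is already planned. The landmark loses patients who recover before week 5. With a constant weekly chance of recovery and a proportion p recovered by week 14, the share lost is 1 − (1 − p)^(5/14): 7.7%, 16.7% or 27.9% for p = 20, 40 or 60%. If all 72 patients were in the model, that is about 6, 12 or 20.

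### The Bonferroni divisor for the recovery models counts only predictors that pass a p < 0.05 screen, so the correction does not give the error control its name implies

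*Protocol article*

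**What the plan says.** The rule is in the Statistical analysis section of the Protocol article.

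- **Recovery models.** There are two: "Separate models will be generated for transitions from UWS to MCS and from MCS to the fully conscious state". The candidates are "measurement time (weeks), traumatic vs. non-traumatic aetiology, age at injury, and complications (yes/no or number"), tried singly: "Independent variables that will be added one by one to the models". Then: "Significant predictors (*p* < 0.05) will be included in a multivariable model using a Bonferonni correction". The correction is defined as "dividing the significance level (alpha< 0.05) by the number of predictors included in the model".
- **Quality of life and participation models.** There are three outcomes: EQ-5D-5L, QOLIBRI and CIQ. The candidates begin "The effects of time, cognitive (MoCa), behavioural (NPI), emotional (HADS), and motor status (FIM), and level of disability (DRS) and discomfort (NCS"), which makes seven. The same p < 0.05 screen applies, followed by a multivariable model "to study the independence of these potential predictors on the outcomes using the Bonferroni correction". The divisor is not restated here.

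The section gives no target error rate for the set of predictors. It names the correction and, for the recovery models, defines its divisor.

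**The concern.** Bonferroni bounds the chance of any false positive because it divides alpha by the number of hypotheses tested. Here, 4 (or 7) hypotheses are tested at the screen, and the divisor then shrinks to however many passed. Candidates that failed the screen were tested too, but they no longer count. The adjustment is weakest when few candidates pass, which is what happens when little or nothing is real.

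The threshold for one predictor also depends on which others happened to pass, so neither it nor the error rate is fixed in advance. This matters because the Background lists predictors of recovery among the main outcomes and the Discussion expects the results to improve prediction of outcome. A predictor reported as Bonferroni-significant would be read as having survived a correction for all candidates examined.

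**Working it through.** The plan states no family-wise error rate, so there is no figure to reproduce. The check is the error rate of the rule as written.

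**Inputs (Statistical analysis section).** Screen at 0.05; divisor equal to the number of predictors in the multivariable model; 4 candidates for recovery; 7 for quality of life and participation. The planned sample of 72 (Data collection) is used only in the simulation.

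**Assumptions.** Candidates are independent, a null candidate has the same p-value in the screen and in the multivariable model, and t true predictors always pass the screen. With m₀ null candidates, the number k that pass is Binomial(m₀, 0.05). A null that has passed has a p-value uniform on (0, 0.05), so it falls below 0.05/(k + t) with probability 1/(k + t). Hence

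P(at least one false predictor) = Σₖ C(m₀,k) · 0.05ᵏ · 0.95^(m₀−k) · [1 − (1 − 1/(k+t))ᵏ].

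**Four candidates, none real (m₀ = 4, t = 0).**
- k = 1: 0.1715 × 1 = 0.1715
- k = 2: 0.01354 × 0.75 = 0.0102
- k = 3: 0.000475 × 0.704 = 0.0003
- k = 4: negligible
- Sum: **0.182**. With no correction: 1 − 0.95⁴ = 0.185.

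A lone survivor accounts for 0.1715/0.1855 = 92% of the cases in which anything passes.

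**Only time real and retained (m₀ = 3, t = 1).** 0.1354 × 1/2 + 0.007125 × 5/9 + 0.000125 × 0.578 = 0.0677 + 0.0040 + 0.0001 = **0.072**.

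**Two real and retained (m₀ = 2, t = 2).** 0.095 × 1/3 + 0.0025 × 0.4375 = **0.033**.

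**Three real and retained (m₀ = 1, t = 3).** 0.05 × 1/4 = **0.0125**.

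Retention matters. If two candidates are real but only one passes the screen, the rate is 0.095/2 + 0.0025 × 0.556 = 0.049. If neither passes, it is 0.095 + 0.0025 × 0.75 = 0.097.

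**Seven candidates, if the same divisor applies.**

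| Truly predictive and retained | Rate |
|---|---|
| 0 | 0.290 (uncorrected: 1 − 0.95⁷ = 0.302) |
| 1 (time) | 0.134 |
| 2 | 0.078 |
| 3 | 0.048 |

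**Dividing by the number tested, none real.** 1 − (1 − 0.05/4)⁴ = 0.049 and 1 − (1 − 0.05/7)⁷ = 0.049.

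**Correlated candidates.** A simulation of the screen followed by the multivariable model (20,000 runs, n = 72, no true predictor, ordinary regression in place of GEE) gave:

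| Correlation | 4 candidates, rule as written | 4, divided by number tested | 7 candidates, rule as written | 7, divided by number tested |
|---|---|---|---|---|
| 0 | 0.177 | 0.051 | 0.288 | 0.048 |
| 0.3 | 0.156 | 0.037 | 0.228 | 0.030 |
| 0.6 | 0.105 | 0.020 | 0.137 | 0.009 |

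Correlation lowers the rates, but with no true predictor they stay well above 0.05 under the written rule.

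**The case against.** The strongest reply is that the worst case is unlikely here. For recovery, time is itself a candidate, and the Background reports recovery after traumatic injury rising from 38% at 3 months to 78% at 12 months. It also lists younger age and traumatic aetiology as prognostic, although one cited study found similar outcomes for traumatic and non-traumatic UWS. If three of the four are real and retained, the rate is about 1%. For quality of life, several candidates overlap with the content of the EQ-5D-5L: FIM with daily activities, NCS with pain, HADS with anxiety and depression. Three real predictors out of seven is therefore plausible. The study is also an observational cohort with no treatment claim resting on a predictor p-value, so strict family-wise control is optional.

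Most of this stands, and it limits the size and severity of the point. It does not rescue the rule, because error control that holds only if enough candidates are real, and also pass the screen, is not control.

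Four stronger readings are not supported:
- **That the plan promises a 5% false-predictor rate and breaks it.** It never says so; control is only implied by the term Bonferroni.
- **That 18% or 29% is the expected rate.** These are upper cases with no true predictor, and the 29% also rests on an inferred divisor.
- **That the per-model rates can be multiplied over the two recovery and three quality-of-life and participation models.** These models share patients, and a five-model figure cannot be set against a per-model 5%: five correctly corrected models would give 1 − 0.95⁵ = 22.6% by the same arithmetic.
- **That penalised estimation is required.** That is a modelling preference.

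**Conclusion.** The point holds as a should-fix matter. The document fixes the divisor for the recovery models in words, and that divisor lacks the property its name implies. Per recovery model, the chance of a false corrected predictor is about 18% if no candidate is real, about 7% if only time is, and below 5% once at least two of four are real and retained. For the quality-of-life and participation models the corresponding figures are about 29%, 13%, and below 5% with at least three of seven real and retained, provided the same divisor is intended.

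These are per-model rates for independent candidates whose screening and adjusted p-values coincide. Correlation among candidates lowers them. So does a strong true predictor that makes the two p-values diverge, because a null must then pass two different tests. The true rate is unknown because it depends on effects the study is meant to estimate.

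**What to change.** State that any Bonferroni or Holm correction is based on the prespecified number of candidates tested: 4 in each recovery model and 7 in each quality-of-life and participation model. State the divisor in the quality-of-life paragraph too. Fix the coding of complications (yes/no or number) in advance; if both are tried, the recovery count is 5.

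Preferably, drop the univariable screen. Fit one prespecified model per outcome with all named candidates and report adjusted estimates with confidence intervals. This also keeps predictors that show an effect only after adjustment.

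The edit is about two sentences and needs no new data. The cost is a stricter threshold (0.0125 or 0.0071 under Bonferroni, never looser than the current rule) and so fewer significant predictors. The full models also estimate more coefficients from at most 72 patients, so intervals may be wider.
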